## Abstract

**Background:**

Patients with type 2 diabetes have 2–4 times greater risk for cardiovascular morbidity and mortality than those without, and this is even further aggravated if they also suffer from hypertension. Unfortunately, less than one third of hypertensive diabetic patients meet blood pressure targets, and more than half fail to achieve target HbA1c values. Thus, appropriate blood pressure and glucose control are of utmost importance. Since treatment sometimes fails in clinical practice while clinical trials generally suggest good efficacy, data from daily clinical practice, especially with regard to the use of newly developed anti-diabetic and anti-hypertensive compounds in unselected patient populations, are essential. The DIALOGUE registry aims to close this important gap by evaluating different treatment approaches in hypertensive type 2 diabetic patients with respect to their effectiveness and tolerability and their impact on outcomes. In addition, DIALOGUE is the first registry to determine treatment success based on the new individualized treatment targets recommended by the ADA and the EASD.

**Methods:**

DIALOGUE is a prospective observational German multicentre registry and will enrol 10,000 patients with both diabetes and hypertension in up to 700 sites. After a baseline visit, further documentations are scheduled at 6, 12 and 24 months. There are two co-primary objectives referring to the most recent guidelines for the treatment of diabetes and hypertension: 1) individual HbA1c goal achievement with respect to anti-diabetic pharmacotherapy and 2) individual blood pressure goal achievement with different antihypertensive treatments. Among the secondary objectives the rate of major cardio-vascular and cerebro-vascular events (MACCE) and the rate of hospitalizations are the most important.

**Conclusion:**

The registry will be able to gain insights into the reasons for the obvious gap between the demonstrated efficacy and safety of anti-diabetic and anti-hypertensive drugs in clinical trials and their real world balance of effectiveness and safety.

## Background

There is an increasing prevalence of type-2 diabetes, which is attributable to a growing population, an increase in life expectancy, increased diagnostic efforts, and a reduced diabetes attributable risk due to recent advances in diabetes treatment 
[1]. Hypertension is the most frequent (90%) among the co-morbid disease conditions 
[2] and further increases the risk for disease and treatment related complications 
[3]. The combination of both hypertension and diabetes accelerates the progression of diabetes related complications such as diabetic nephropathy, retinopathy, left ventricular hypertrophy, and diastolic heart failure and doubles the risk of stroke, CV and all-cause mortality as compared to non-diabetic patients with hypertension. Risk prediction in this population is however not easy making the adaption of available risk prediction tools necessary, partly because risks have gone down in recent years 
[4].

### Glucose and blood pressure control

A number of studies have shown improved glycaemic control to be able to delay the onset and also to halt the progression of micro-vascular complications such as diabetic retinopathy and nephropathy. This has also been shown for neuropathic secondary disorders 
[5,6]. For macro-vascular complications, however, the picture to date is less straightforward. There is doubt as to whether the benefit of tight glycaemic control on macro-vascular events is as great as the one effected by blood pressure and lipid control. A recent meta-analysis of five large trials 
[7] found a significant reduction in event rates for non-fatal myocardial infarction and also for CAD, but all-cause mortality and stroke rates were not similarly affected.

An exploratory analysis of the United Kingdom Prospective Diabetes Study (UKPDS) data showed that the risk of both micro- and macro-vascular complications of type 2 diabetes (T2D) was strongly associated with the mean systolic blood pressure and that blood pressure lowering by 10 mmHg led to a 15 % reduction in the risk for death related to diabetes 
[8].

In the Steno-2 study, intensified therapy of the modifiable risk factors in patients with T2D and microalbuminuria was compared to standard treatment. In addition to lifestyle changes and diet modifications, all patients in this group received ACE-inhibitors (ACEI) or angiotensin receptor blockers (ARB) irrespective of baseline BP values and a vitamin-mineral supplement. The target limits for HbA1c, fasting cholesterol and triglycerides and blood pressure were much stricter than in the control group. This multi-factorial approach led to significant reductions in both micro- and macro-vascular event rates 
[9,10].

Thus, in diabetic patients with hypertension, appropriate blood pressure control as well as glucose control is important. Current guidelines 
[11,12] recommend a multi-factorial approach with simultaneous targeting of blood pressure and glucose levels. Unfortunately, less than one third of the hypertensive diabetics meet their blood pressure targets and less than half of them their HbA1c target.

### Pharmacotherapy

During recent years new medications and fixed dose combinations have been developed for the treatment of T2D and hypertension. For achieving glycaemic control, a number of oral therapeutic options are available, using different approaches. There are agents that increase insulin secretion, such that improve insulin action and also substances delaying carbohydrate absorption. Unfortunately, most of them – with the exception of metformin – are associated with weight gain. Hypoglycaemia and in some cases gastrointestinal side effects and oedema are other possible disadvantages. Another issue is the failure to achieve adequate control of postprandial blood glucose and also long term glycaemic control 
[13]. In recent years, incretin-based treatments like DPP-4 inhibitors (Vildagliptin, Sitagliptin, Saxagliptin, Linagliptin) have been shown to be a potent strategy and are increasingly used in fixed dose combinations (e.g. with metformin) 
[14-18]. As these drugs display different properties, e.g. pharmacokinetics, they influence the glycaemic profile in T2D – patients in different ways. This may be measure by the Mean Amplitude of Glycaemic Excursions (MAGE) and Rizzo confirmed that MAGE reduction was associated with reduction of oxidative stress and markers of systemic inflammation in T2D patients 
[19]. Since glucose variations over time, linked to circadian fluctuations of glucose levels, are associated with an activation of oxidative stress, the main mechanisms that lead to chronic diabetic complications 
[20], these data suggest that any therapy should aim not only to reduce HbA1c but also to flatten acute glucose fluctuations over time to positively influence the outcome of T2D patients.

To achieve adequate blood pressure control, an even larger number of therapy options exist. As diabetic patients frequently also have impaired renal function associated with microalbuminuria, substances affecting the renin-angiotensin system, which are known to display renal benefits independent of blood pressure reduction, appear to be particularly beneficial 
[21-23]. ACEI and ARB are available in several fixed dose combinations with calcium channel blockers like amlodipine and/or diuretics like hydrochlorothiazide. Interestingly, the use of fixed dose combinations has been shown to significantly improve compliance by reducing pill burden 
[24,25], which results in higher rates of treatment target achievement and lower hospitalisation rates.

### Guideline compliance in daily clinical practice

Treatment recommendations by current guidelines are mainly based on evidence from randomised controlled trials. However, these trials reflect only selected patient populations defined by detailed in- and exclusion criteria of these trials. Patients in daily practice are usually older and suffer from more co-morbidities as compared to those in clinical trials 
[26,27]. Available data suggest suboptimal treatment target achievement with respect to glucose, blood pressure and lipid control 
[28-31]. While there are quite some data on patient characteristics, current treatments and outcome of diabetics with hypertension in clinical practice, there are much less especially with respect to the use of newly developed and approved anti-hypertensive and anti-diabetic compounds and physicians approach towards its management 
[32]. Additionally, it is quite unclear if and how the different combinations of anti-diabetic and anti-hypertensive medications contribute to the achievement and preservation of target blood glucose and blood pressure values in individual patients.

### Aim

The purpose of the registry is to evaluate various therapy regimes of anti-diabetic (including incretin-based and exclusively non-incretin-based therapies) and anti-hypertensive treatments (including RAAS-inhibitors and exclusively non-RAAS-inhibitors) as well as their combinations, patient reported outcomes and treatment success in hypertensive T2D patients. It is the first prospective registry to determine treatment success based on the new individualized treatment targets of the ADA and the EASD 
[33].

## Methods/Design

DIALOGUE is a prospective observational national multicentre registry with a follow-up of 24 months and will enrol 10,000 patients with both T2D and hypertension from up to 700 sites in Germany. Data are recorded at baseline and will be prospectively documented during follow up visits at 6, 12 and 24 months.

This registry is conducted in accordance with the ethical principles that have their origin in the Declaration of Helsinki and adhere to the principles of Good Epidemiology Practice (GEP), and applicable regulatory requirements. The protocol of this registry was approved by the ethics committee of the Ruhr University Bochum, Germany. Patients that being enrolled into this registry will provide written informed consent. DIALOGUE has further been registered in the database of the *Verband forschender Arzneimittelhersteller* (VFA).

### Primary objective

The two co-primary objectives are: 1) documentation of individual HbA1c goal achievement with respect to anti-diabetic pharmacotherapy and 2) documentation of individual blood pressure goal achievement with different anti-hypertensive treatments.

### Secondary objective

Secondary objectives are (1) to document major cardio-vascular and cerebro-vascular events (MACCE) during 2 year follow-up; (2) to document hospitalizations during 2 year follow-up; (3) to assess the proportion of patients reaching blood glucose target values without experiencing the following adverse effects: peripheral oedema or proven hypoglycaemic events or discontinuation due to gastrointestinal events or significant weight gain (>5 %); (4) to describe patient characteristics in patients with diabetes mellitus and hypertension in clinical practice in the overall registry population; (5) to document anti-diabetic and anti-hypertensive therapy and its impact on treatment target achievements in diverse subject populations, which have to be pre-specified by the scientific committee (e.g. females versus males, age </>75y, patients on insulin versus patients not on insulin, etc.); (6) to verify the applicability of and the adherence to the current guidelines for the treatment of diabetes and hypertension in clinical practice; (7) to document utilisation patterns of drugs used for the treatment of diabetes as well as hypertension in clinical practice; (8) To evaluate adverse cardio-vascular events as well as diabetes-related micro-vascular and macro-vascular events; (9) to evaluate the glycaemic profiles of the participants with regards to differences in anti-diabetic treatment patterns; (10) to evaluate the blood pressure profiles; (11) To evaluate co-morbid disease conditions; (12) to evaluate the change in BMI over the course of the study; (13) to evaluate the proportion of patients with hypoglycaemic events over the course of the follow-up; (14) to evaluate cardio-vascular risk by using validated cardio-vascular risk scores such as the EURO Score; (15) to evaluate health status (EQ-5D); (16) to determine costs associated with the treatment and disease related complications; (17) to document treatment persistence over time, change in treatments / dosing during a follow-up of two years (optional up to 4 years of follow-up); (18) to document patient reported outcome (PRO).

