### Documented variables

Table 
1 gives an overview of the variables to be documented. Source documentation and data accuracy will be verified by site visits in randomly selected 2% of the sites.

**Table 1 T1:** Overview of documented parameters

**Visit**	**Baseline**	**FU 6 mo**	**FU 12 mo**	**FU 24 mo**
Sociodemographics ^1^	x			
Physical examination ^2^	x			
Cardiovascular concomitant diseases ^3^	x	x	x	x
Diabetes associated diseases ^4^	x	x	x	x
Available laboratory values^5^	x	x	x	x
Antidiabetic medication^6^	x	x	x	x
Additional current medication	x	x	x	x
Hypoglycaemic events^8^	x	x	x	x
QoL (EuroQoL-5D)	x	x	x	x
Patient reported outcomes (PRO)	x	x	x	x

*Legend:* 1) age, gender, insurance status, DMP participation, education, employment status, care level 2) weight, height, waist circumference, smoking, alcohol consumption, physical activity 3) coronary heart disease, previous myocardial infarction, previous PCI, previous CABG, previous stroke, heart failure (NYHA) peripheral artery occlusive disease 4) dyslipidemia, amputation, autonomous neuropathy, non- proliferative/proliferative retinopathy, diabetic macular edema, blindness, dialysis other 5) less than six weeks old: lipid values (fasting total cholesterol, fasting LDL, fasting HDL, triglycerides), fasting and post-prandial blood glucose, HbA1c, renal values (serum creatinine, microalbustix albumin, microalbustix creatinine), liver parameters. 6) metformin, sufonylureas, glucosidase inhibitors, glinides, glitazones, DPP-4 inhibitors) 7) ACE inhibitors, ARBs, renin inhibitors, beta blockers, calcium channel blockers, diuretics, other) 8) 12 months before baseline visit and since baseline or last FU, respectively.

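### Table 1 schedules weight at baseline only, which contradicts the two secondary objectives that need a follow-up weight (BMI change and freedom from weight gain above 5%)

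*Protocol article*

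**What the plan says.** The article's Secondary objective section lists 18 items. Two depend on weight over time.

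- Item 12 is "to evaluate the change in BMI over the course of the study".
- Item 3 is "to assess the proportion of patients reaching blood glucose target values without experiencing the following adverse effects", and the list of adverse effects that follows ends with "discontinuation due to gastrointestinal events or significant weight gain", the weight gain being set at more than 5%.

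The Documented variables section gives the visit schedule in Table 1, with columns for baseline and for follow-up at 6, 12 and 24 months. Weight and height sit in the row "Physical examination ^2", whose footnote reads "2) weight, height, waist circumference, smoking, alcohol consumption, physical activity". That row has a mark at baseline and empty cells at all three follow-up visits.

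**The concern.** A change in BMI and a percentage weight gain both compare a later weight with an earlier one. A schedule that measures weight once supplies no comparison. If the case report form follows Table 1, objective 12 has no data. The composite in objective 3 also cannot be determined as defined, because success requires every listed harm to be absent and one of them would be unmeasured.

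Weight is not a marginal item here. The Pharmacotherapy section says that most oral glucose-lowering options other than metformin are associated with weight gain. The registry sets out to describe different drug regimens in routine care, so weight is a tolerability outcome that the article itself treats as relevant to the choice between them.

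**Working it through.** No sample size, power or event figure bears on this point, and the plan states no figure to reproduce. The check is a reading of the objectives against each row and footnote of Table 1, followed by a search of the rest of the article for another source of follow-up weight.

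**What each objective needs**

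- BMI change at visit t: BMI(t) − BMI(0), with BMI = weight / height². In adults one height is enough, so the requirement is weight at baseline and at visit t.
- Weight gain above 5% at visit t: [weight(t) − weight(0)] / weight(0) > 0.05. The requirement is the same two weights.

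Each therefore needs at least 2 weights per patient.

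**What Table 1 supplies**

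| Rows of Table 1 | Baseline | 6 mo | 12 mo | 24 mo | Weight or BMI in the footnote? |
|---|---|---|---|---|---|
| Sociodemographics | x | – | – | – | no |
| Physical examination | x | – | – | – | **yes: weight and height** |
| The other eight rows | x | x | x | x | no |

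The eight rows marked at every visit are cardiovascular concomitant diseases, diabetes-associated diseases, laboratory values, antidiabetic medication, other medication, hypoglycaemic events, quality of life and patient-reported outcomes. The row "Available laboratory values^5" shows that the table marks repeat measurement where it is meant.

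Scheduled weights per patient: 1 of 4 visits overall, and 0 of 3 at follow-up. Since 1 < 2, neither quantity can be computed at 6, 12 or 24 months from this schedule.

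**Is there another source?**

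- The opening of Methods/Design says in general terms that data are documented at the three follow-up visits, but does not name weight.
- Statistical methods takes its data from the electronic case report form, the quality-of-life assessments and parameters derived from them. A derived BMI change still needs a second weight as input.
- No other section mentions a follow-up weight or BMI.

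**Could this be a reading error?** Unlikely. The empty cells of the Physical examination row are intact in the table, and they match the pattern of the sociodemographic row above it.

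**The case against.** The strongest reply is that Table 1 is incomplete, so little should be built on it. The text calls it an overview, and it stands in a journal article that condenses a longer protocol. It has no entry for blood pressure, although blood pressure goal achievement is a co-primary objective, and none for hospitalisations or costs. Its legend defines a footnote 7, on antihypertensive drugs, that no row carries. The registry can hardly intend to record no blood pressure, so the case report form probably holds more than the table shows, and follow-up weight may be among it.

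This stands in part. It rules out the claim that the registry will have no follow-up weights. It does not remove the contradiction, because weight differs from an item the table omits: it has a row, the row has follow-up columns, and those cells are blank. The article states a schedule for weight, and that schedule conflicts with its own objectives. This is more than a detail left to the analysis plan.

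A reader might go further in three ways that the document does not support.

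- *Oedema and gastrointestinal discontinuation are not recorded either, so the composite reduces to reaching target without hypoglycaemia.* These items merely lack a row in a condensed table. Medication is marked at every visit, so discontinuation can at least be seen.
- *Unmeasured harms will be counted as absent, which favours drugs that raise weight.* The article does not say how a missing component of the composite is handled.
- *Composite success will be overstated by some percentage.* The article gives no frequency of weight gain above 5%, nor its overlap with the other harms, so any such figure would be invented.

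It is also fair to say that these are secondary objectives in a registry without formal tests, and that the abstract ranks cardiovascular and cerebrovascular events and hospitalisations as the most important secondary objectives.

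**Conclusion.** The point holds as an inconsistency between the stated objectives and the stated schedule. Under Table 1 as published, 0 of 3 follow-up visits supply a weight, so BMI change (objective 12) and the weight-gain component of objective 3 cannot be derived.

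The conclusion is limited to the published schedule. It assumes that the blank cells mean not collected. If the case report form does collect follow-up weight, the table is wrong and the objectives can be met. Either way, one of the two sections needs correction.

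Two of 18 secondary objectives are affected, and neither co-primary objective is. The effect on any estimate cannot be sized from the document. This should be fixed, but it does not undermine the registry's main purpose.

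**What to change.** First check the case report form, then take one of three routes.

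1. If follow-up weight is not collected, add a weight field at 6, 12 and 24 months and mark it in Table 1 as a row of its own. Height carries forward from baseline, and the other items of the Physical examination row can stay at baseline.
2. If follow-up weight is already collected, correct Table 1 to show it.
3. If follow-up weight will not be collected, amend objective 12 and the weight-gain component of objective 3 so that neither relies on a measurement the registry does not make.

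The cost of the first route is one extra field per follow-up visit, three per patient over 24 months. The second and third change text only.

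Timing matters for the first route. The Recruitment plan puts the start of enrolment in July 2012, so the earliest 6-month visits fall around January 2013, and a weight not recorded at a visit may not be recoverable later.

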### Selection of sites

The registry will be performed in primary care and diabetes centres in Germany, with a planned participation of up to 700 sites. Centres will be selected from a database maintained at the *Institut für Herzinfarktforschung* to be representative for the ambulatory treatment of diabetes and hypertension in Germany. For this purpose, a representative cross-section of different types of centres including diabetologists and primary care physicians will be built. The sampling strategy will thus provide a representative dataset for the description of oral anti-diabetic treatment patterns in Germany.

### Selection of patients

Inclusion criteria are as follows: 1) Age: ≥18 years 2) Diagnosed type 2 diabetes mellitus and manifest hypertension (comorbidity) 3) Antidiabetic therapy presently on oral mono- or dual combination therapy (no insulin, no GLP-1 analogue) 4) The treating physician considers blood glucose lowering medication to be not adequate and/or not safe/tolerable 5) The physician adds another oral drug / switches drug treatment to achieve glycaemic control 6) Written informed consent for participation obtained from the subject.

Patients will not be eligible for inclusion if any of the following exclusion criteria apply: 1.) Current participation in any randomised controlled trial. 2) Patients not under regular supervision of the treating physician for the duration of the study 3) Use of GLP-1-analogues or insulin before enrolment 4) Patients treated with aliskiren in a dual renin angiotensin aldosterone (RAAS) blockade 5) Pregnancy 6) Diabetes secondary to malnutrition, infection or surgery 7) Maturity onset diabetes of the young 8) Known cancer.

Patients will be enrolled according to a pre-specified ratio based on their treatment, which is not pre-determined by the study protocol but based on the physician’s decision (Figure 
1). “Incretin-based treatment” is defined as either a DPP-4 inhibitor or a GLP-1 analogue. “Non-incretin-based treatment” is defined as any of the following: metformin, sulfonylureas, acarbose, insulin, alpha-glucosidase inhibitors, and/or SGLT2-inhibitors. As the clinical profile of vildagliptin appears to differ from that of other DPP-4 inhibitors, the “incretin-based treatment” group will be split into those with or without vildagliptin.

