**Figure 1 F1:**
[figure not shown]
**Sample size and segmentation into strata of different antidiabetic-treatments.***Legend:* Patients are eligible for inclusion if treated with oral mono or dual combination therapy and are distributed into the following groups: Incretin-based treatments include DPP-4 inhibitors and GLP-1 analogues. Non-incretin-based therapies include metformin, sulfonylureas, acarbose, insulin, alpha-glucosidase inhibitors, and SGLT2-inhibitors.

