### Statistical methods

All variables collected in the eCRF as well as the data obtained from the quality of life assessments and all derived parameters will be used in the statistical analysis. Binary, categorical, and ordinal parameters will be summarised by means of absolute and percentage numbers within the various categories (including ‘missing data’ as valid category at baseline). Numerical data will be summarised by means of standard statistics (i.e. number of available data, number of missing data, mean, standard deviation, minimum, median, maximum, lower and upper quartile). In addition, adequate graphs (e.g. bar charts, box-whisker plots) may be presented to summarise the results for some parameters. Time-to-event variables will be analysed via a Cox proportional hazard regression model presenting hazard ratios and the corresponding 95% confidence intervals. In addition Kaplan-Meier curves will be presented for these variables. Two-sided 95%-CI will be presented for important parameters, but should be interpreted in an exploratory descriptive way. Further multivariable analyses will be performed according to the statistical analysis plan (SAP). Formal statistical tests will not be performed within the statistical analysis. A report including descriptive statistics of all documented parameters will be generated for the overall patient population. Depending on the variable(s) of interest, additional selection criteria for patients (e.g. subgroup analyses) considered in specific analyses may be used, if considered useful during the statistical analysis. Details on the selection criteria used will be given in the SAP and in the statistical section of the report. The statistical analysis will be performed using SAS (release 9.2 or higher; Cary, NC, USA).

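### Enrolment to a pre-specified treatment ratio fixes the anti-diabetic class shares at baseline, so the claim of representative treatment patterns does not hold for them

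*Protocol article*

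**What the plan says.** Selection of sites describes how centres are drawn from an existing database to reflect ambulatory care, with a mix of diabetologists and primary care physicians. It concludes: "The sampling strategy will thus provide a representative dataset for the description of oral anti-diabetic treatment patterns in Germany".

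Selection of patients then sets a second rule, at patient level: "Patients will be enrolled according to a pre-specified ratio based on their treatment". Of the treatment it adds "which is not pre-determined by the study protocol but based on the physician’s decision". The classes are incretin-based and non-incretin-based, and "the “incretin-based treatment” group will be split into those with or without vildagliptin". The title of Figure 1 points the same way: "Sample size and segmentation into strata of different antidiabetic-treatments". The inclusion criteria also limit entry to patients on one or two oral drugs whose physician finds that treatment inadequate or not safe or tolerable and is changing it.

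Secondary objective 7 is "to document utilisation patterns of drugs used for the treatment of diabetes as well as hypertension in clinical practice". Secondary objective 4 describes patient characteristics in clinical practice, in the whole registry population. Under Statistical methods: "A report including descriptive statistics of all documented parameters will be generated for the overall patient population". The first co-primary objective concerns HbA1c goal achievement in relation to anti-diabetic drug treatment.

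**The concern.** The representativeness claim rests on centre selection alone. Representative centres would give representative treatment patterns if each centre enrolled its eligible patients as they came. Here the number entering in each treatment class follows a ratio fixed beforehand, and treatment class is the variable to be described. A baseline table of the shares on DPP-4 inhibitors, on vildagliptin or on neither would largely return the design ratio, yet a reader of the final report could take it for German prescribing.

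Pooled figures inherit the problem indirectly. Any characteristic or outcome that differs between treatment classes is averaged with the ratio as its weights. With 10,000 patients the confidence interval would be narrow, so a modest shift could lie outside it.

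**Working it through.** **1. The two statements side by side.** The conclusion under Selection of sites uses only the sampling of centres. Selection of patients samples on treatment class within those centres. The physician chooses each patient's drug, but the ratio governs how many patients on each class are enrolled. If it is kept, the enrolled class shares equal the ratio whatever happens in practice. This step needs neither the value of the ratio nor the SAP.

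**2. Inputs for the size.** The article gives no figure to reproduce: the 10,000 comes without a precision or power calculation. From the article: N = 10,000. Assumed, and simplified to two strata:
- q, the incretin share set by the ratio: 50 % or 70 %
- s, the incretin share among eligible patients in practice: 30 %
- d, the difference in goal achievement between strata: 5 or 10 points, with 45 % in the non-incretin stratum

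**3. Error in a class share** = q − s.
- 50 − 30 = 20 points
- 70 − 30 = 40 points

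The error is zero if q = s and changes sign if practice exceeds the ratio: with q = 50 % and s = 60 % it is −10 points.

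**4. Shift in a pooled, unweighted proportion** = (q − s) × d. Coverage is the chance that the nominal 95 % interval contains the value in practice (normal approximation, N = 10,000).

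| q | s | d | Shift | Coverage |
|---|---|---|---|---|
| 0.50 | 0.30 | 0.05 | 0.20 × 0.05 = 1.0 point | 48 % |
| 0.50 | 0.30 | 0.10 | 0.20 × 0.10 = 2.0 points | 2 % |
| 0.70 | 0.30 | 0.05 | 0.40 × 0.05 = 2.0 points | 2 % |
| 0.70 | 0.30 | 0.10 | 0.40 × 0.10 = 4.0 points | about 0 % |

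For comparison, the 95 % half-width near 50 % is 1.96 × √(0.25 / 10,000) = 0.98 points.

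**5. Price of weighting.** With weights s/q and (1 − s)/(1 − q), the Kish effective sample size is N / [q(s/q)² + (1 − q)((1 − s)/(1 − q))²].
- q = 0.50, s = 0.30: 10,000 / (0.5 × 0.6² + 0.5 × 1.4²) = 10,000 / 1.16 = 8,621
- q = 0.70, s = 0.30: 10,000 / 1.762 = 5,676

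Weighting would remove the shift due to the ratio at a tolerable cost in precision, but it needs a value for s. The article names no source for one.

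**The case against.** A ratio by treatment is an ordinary way to secure enough patients per stratum, and the first co-primary objective is already framed by anti-diabetic treatment. That stands: the ratio does not by itself bias results within a stratum. A reader might infer that the registry cannot give valid overall results or that its primary aims are compromised. The article does not support either inference.

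A reader might also take the pooled analysis to be unweighted. Statistical methods does not say so, and the SAP, which is not shown, may provide weights. The point on pooled figures is therefore conditional. The point on class shares at enrolment is not, because the sentence under Selection of sites is wrong as it stands.

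The clause that treatment is the physician's decision might seem to remove the ratio. It most naturally describes the choice of treatment, not the choice of whom to enrol. Nor does the article say who set the ratio, so attributing it to the sponsor would go beyond the text.

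Objective 7 also covers anti-hypertensive drugs, which carry no ratio. They are affected only so far as they differ by anti-diabetic class. Medication is also recorded at 6, 12 and 24 months, so later switching and persistence can still be described. The Abstract's phrase "in unselected patient populations, are essential" says what kind of data is needed; it does not claim that this sample is unselected.

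Finally, the size is entirely assumed. The half-width of 0.98 points also ignores attrition and clustering. With 10,000 / 700 ≈ 14 patients per site and an assumed intraclass correlation of 0.05, it becomes 0.98 × √(1 + 13 × 0.05) ≈ 1.3 points, so the smallest shift in the table would lie inside it.

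**Conclusion.** The claim of a representative dataset for oral anti-diabetic treatment patterns contradicts the enrolment rule. Shares of incretin-based, vildagliptin and non-incretin-based treatment at enrolment are fixed by design and cannot be reported as German utilisation. The claim also omits that only patients whose oral therapy is being changed can enter. Pooled descriptions carry the enrolled mix unless weighted.

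The contradiction is certain from the text; its size is not. Under the stated assumptions it is 20–40 points in a class share and 1–4 points in pooled goal achievement. It is nil if the ratio happens to mirror practice, which the article does not say. The point should be corrected, but it touches secondary descriptive aims and leaves comparisons within strata intact.

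**What to change.** - Under Selection of sites, limit the representativeness claim to the mix of centres and withdraw it for anti-diabetic class shares. State there that only patients whose oral therapy is being changed are enrolled.
- Make the tables by treatment stratum the main presentation of patient characteristics and goal achievement.
- Under secondary objective 7, limit anti-diabetic utilisation at enrolment to drug choice within strata. Leave anti-hypertensive utilisation and later switching or persistence as planned.
- Label pooled figures as the enrolled mix, or weight them if a source of the true stratum shares exists. A new log of eligible patients would come late, since enrolment was planned from July 2012 to early 2013, so the fix should not depend on one.

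The cost is wording and table order. The sponsor gives up an overall headline figure as an estimate of German practice. If weights are used, precision falls as shown in step 5 of the check.
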